#### 7.1.3 Other study parameters (if applicable)

Not applicable.

### 7.2 Randomisation, blinding and treatment allocation

The study is a single-centre, open-label Phase II clinical AKS-452X booster vaccine-evaluation study. No randomisation is applicable, nor blinding. All subjects included will receive the active vaccine AKS-452 without adjuvant. The Phase II study will comprise 150 subjects per cohort (all subjects will receive the active vaccine).

### 7.3 Study procedures phase I (including booster with naked AKS-452)

- AKS-452X will be mixed with saline at the pharmacy and doses of 90  $\mu\text{g}$  (with a total volume of 150  $\mu\text{L}$ ) will be injected subcutaneously.
- In the Table below, the Proposed clinical Schedule for phase II is provided.

|                                                                               | Screening Visit | Visit 1 (first dose) | Visit 2        | Visit 3  | Visit 4  | Visit 5   | Visit 6    |
|-------------------------------------------------------------------------------|-----------------|----------------------|----------------|----------|----------|-----------|------------|
|                                                                               | Day -28 to -2   | Day 0                | Day 28±2       | Day 56±2 | Day 91±5 | Day 182±7 | Day 273 ±7 |
| Screening/Administrative/Other Assessments                             |                 |                      |                |          |          |           |            |
| Informed consent                                                              | X               |                      |                |          |          |           |            |
| Demography                                                                    | X               |                      |                |          |          |           |            |
| Eligibility criteria                                                          | X               | X                    |                |          |          |           |            |
| Medical and medication history                                                | X               |                      |                |          |          |           |            |
| Serology a                                                         | X               |                      |                |          |          |           |            |
| Drug screen b                                                      | X               | X                    |                |          |          |           |            |
| COVID-19 PCR                                                                  | X               | X                    |                |          |          |           |            |
| Safety Assessments                                                     |                 |                      |                |          |          |           |            |
| Physical exam                                                                 | X               |                      |                |          |          |           |            |
| Vital signs                                                                   | X               | X                    |                |          |          |           |            |
| Blood pregnancy test c                                             | X               |                      |                |          |          |           |            |
| Urine pregnancy test c                                             |                 | X                    |                |          |          |           |            |
| Blood for safety a                                                 | X               | X                    |                |          |          |           |            |
| Vaccination Questionnaire                                                     |                 |                      | X f |          |          |           |            |
| Concomittant therapy, AEs/SAEs c                                   |                 | X                    | X              | X        | X        | X         | X          |
| Study Agent Administration/Pharmacokinetics and Immunology Assessments |                 |                      |                |          |          |           |            |
| Fc-conjugation vaccine administration d                            |                 | X                    |                |          |          |           |            |
| Peripheral blood for humoral responses                                        |                 | X g       | X              | X        | X        | X         | X          |
| Peripheral blood for PBMCs (cellular responses)                               |                 | X g       | X              |          |          | X         |            |

a) See Laboratory assessments for list of tests.

b) Using instant urine drug test kit

c) In all women

d) After vaccination, subjects are to be kept under medical supervision for 15 min.

e) Subjects who terminate the study early will be asked to return to the clinical site within 14 days after discontinuation for safety assessments

f) To be taken on paper. Subjects will be asked to log all (non-important) AE's between visits

g) Sample to be taken pre-vaccine administration

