### 3. STUDY DESIGN

The study is designed as a single-center open-label phase II clinical study design:

Single center, open-label, safety and efficacy study on the biological activity of a SP/RBD-Fc antigen booster vaccine (AKS-452) against COVID-19.

**Study population:** Healthy human volunteers, 18 - 85 years, having received a registered vaccine (i.e. Pfizer [Comirnaty], Moderna [Spikevax], Janssen [Ad26.COV2.S], AstraZeneca [Vaxzevria]).

In the executed phase I study, an amendment to booster subjects with naked AKS-452 who received a single-dose injection of AKS-452 with adjuvant Montanide ISA 720 as vaccine (i.e. cohort 1: 22.5 µg, cohort 3: 45 µg, and cohort 5: 90 µg), was recently granted by the Dutch CCMO and is currently underway. The complete study will have a duration of approximately 9-12 months and will be executed by TRACER BV on behalf of Akston Biosciences in the University Medical Center Groningen (UMCG), The Netherlands, on behalf of Akston Biosciences,

Akston's clinical SP/RBD-Fc vaccine candidate is AKS-452, although Akston has experience with several protein antigen variations that have been initially evaluated in mouse immunization studies for capacity to induce high-titer neutralizing Ab responses using different dosing strategies. Such SP/RBD-Fc proteins have been evaluated as stand-alone vaccines and in formulations containing different adjuvants for screening and selection of a lead adjuvant. Key findings in mice and other species described below in the preclinical experience, Section 1.3. demonstrate the immunogenic effectiveness of the Fc moiety in addition to the strong immunogenic nature of Montanide ISA 720 that supports its use as an adjuvant.

This clinical trial strategy follows those of other organizations currently entering or having finalized Phase III trials with COVID-19 vaccines [20, 31, 49, 50] and more recently boosting with a third dose (A more detailed description of the clinical study design is illustrated in **Figure 7**).

**Anti-COVID19 Vaccination AKS-452X BOOSTER Study (Protocol nr. 901452-CT-21-001)**[figure not shown]

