#### 4.4 Sample size calculation

The study consists of a Phase II clinical study. The following stopping-rule will be applied on a cohort-by-cohort basis: for a particular cohort, any SAE or AE  $\geq 3$  (according to NCI Common Terminology Criteria for Adverse Events [CTCAE]) attributable to AKS-452X.

On the basis of the phase I/II safety assessment data conducted and a minimum project enhanced immune response rate of 80% for each cohort.

Enhanced immune response rate is defined as:

- i) Seroconversion based on a true positive based on the SP/RBD IgG ELISA assay positive/negative cutoff criteria using the quantitative cut-off value defined by the assay kit batch expressed in  $\mu\text{g/mL}$ . The positive/negative cutoff value was established as 2.42  $\mu\text{g/mL}$  from the validation analysis for the current lot of assay kits, but it should be noted that for each new lot of assay kits, Akston QC performs a re-validation of the cutoff value in order to maintain clinical agreement from lot-to-lot, and/or
- ii) Two times (2x) the baseline SP/RBD IgG at day 28 after boosting, as compared to the titer just before vaccination (day 0).

Based on the observed seroconversion rates in phase I/II and the statistical assessment for the phase II ACT-BOOSTER, a total study group of 150 subjects per cohort of registered vaccine (i.e. Pfizer [Comirnaty], Moderna [Spikevax], Janssen [Ad26.COV2.S], AstraZeneca [Vaxzevria]), totalling 600 subjects is regarded statistically significant to confirm the hypothesis. The statistical assessment providing the above stated numbers is based on the following argumentation (see Table 2 and Figure 9).

| Fixed Scenario Elements |                      |
|-------------------------|----------------------|
| Method                  | Normal approximation |
| Number of Sides         | U                    |
| Null Proportion         | 0.7                  |
| Nominal Power           | 0.8                  |
| Variance Estimate       | Null Variance        |
| Alpha                   | 0.05                 |

| Computed N Total |            |              |         |
|------------------|------------|--------------|---------|
| Index            | Proportion | Actual Power | N Total |
| 1                | 0.80       | 0.800        | 119     |
| 2                | 0.82       | 0.802        | 81      |
| 3                | 0.84       | 0.803        | 58      |
| 4                | 0.86       | 0.803        | 43      |

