**Anti-COVID19 Vaccination AKS-452X BOOSTER Study (Protocol nr. 901452-CT-21-001)**

The repeated dose toxicity study in New Zealand White Rabbits revealed that no significant mortality or organ weight changes were observed at the main study termination. Mild effects, such as increases in fibrinogen, were most likely due to the Montanide ISA 720 adjuvant during the Dosing Phase which subsided during the recovery phase. The expected macroscopic and microscopic transient redness of the injection site were also likely due to adjuvant. These findings from the animal toxicity studies on the adjuvant are in line with clinical findings of adverse events in clinical trials. A potential risk is an allergic reaction after the injection of AKS-452X. In this trial, to guard the subjects' safety during and after AKS-452X injection, they will be closely observed until 15 minutes post injection by qualified nurses, who will be ready to promptly intervene.

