#### **7.7 . Premature termination of the study**

Termination based on safety aspects: A multidisciplinary team with study investigators ([co]PI's and dedicated research physicians) together with the sponsor will discuss safety aspects during the study procedures.

The CTCAE stopping rules for first in human studies will be leading to grade a possible SAE and how to proceed if an SAE occurs.

The termination rules are as follows: When an SAE and/or AE  $\geq$  grade 3 NCI CTCAE (attributable to AKS-452X) occurs after the s.c. injection: terminate the study for all cohorts (e.g. if an SAE occurs in cohort 1, 2, 3, or 4, terminate the entire study).

Termination based on other aspects: The study will be suspended based on urgent medical or ethical considerations as decided by the principal investigators (additional to section 8.7). In case of termination of the study, the sponsor, the institution, regulatory authorities (CCMO will be informed. Moreover, sponsor's medical monitor (or designee) may stop or suspend the trial due to safety concerns from the sponsor. Furthermore, sponsor may stop the trial due to other concerns.

Mandatory: A cohort must demonstrate a minimum of 80% seroconversion (in case a subject dropouts before day 28, he/she will be replaced with another subject. A cohort must include a

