### 8.2 AEs, SAEs and SUSARs

#### 8.2.1 Adverse events (AEs)

Adverse events are defined as any undesirable experience occurring to a subject during the study, whether or not considered related to the investigational product / trial procedure / the experimental intervention. All adverse events reported spontaneously by the subject or observed by the investigator or his staff will be recorded. Subjects will be monitored throughout the study for AEs, from the time of first dose on Day 0 up to the assessments of Day 273. Untoward events that occur prior to the booster dose of the study vaccine will not be recorded as an AE but should be recorded as medical history. Adverse events that are identified at the last assessment visit (or the early termination visit) as specified in the protocol must be recorded on the AE CRF with the status of the AE noted, and the AE must be followed until resolution. AEs that are resolved at the final study visit should be recorded with a stop date. All AEs should be followed to resolution whenever possible. Action taken will be categorized as none, study drug discontinued, dose modified, required concomitant medication, required procedure, or other. Event outcome at resolution or time of last evaluation will be recorded as event resolved, resolved with sequelae, ongoing, or death.

**Severity.** For evaluating severity and relatedness to AKS-452X, CTCAE will be used (CTCAE V5.0). Adverse events will be graded by a numerical score according to the defined NCI Common Terminology Criteria for Adverse Events (NCI CTCAE) and version number specified in the protocol. Adverse events not specifically defined in the NCI CTCAE will be scored on the Adverse Event log according to the general guidelines provided by the NCI CTCAE and as outlined below:

- Grade 1: Mild
- Grade 2: Moderate
- Grade 3: Severe or medically significant but not immediately life threatening
- Grade 4: Life threatening consequences
- Grade 5: Death related to the adverse event

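### The stopping rule acts on a single attributable grade 3 event, but no adverse-event contact is scheduled between the 15-minute observation and Day 28, so the rule could be triggered up to about four weeks late

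*Protocol*

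**What the plan says.** **The rule.** Section 4.4 states "The following stopping-rule will be applied on a cohort-by-cohort basis"; its trigger is any SAE, or any AE of CTCAE grade 3 or higher, attributable to AKS-452X. Section 7.7 has the same single-event trigger, with the instruction to "terminate the study for all cohorts".

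**Observation after dosing.** Section 5.4 says of subjects that "they will be closely observed until 15 minutes post injection by qualified nurses". Footnote d of the Section 7.3 schedule gives the same 15 minutes.

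**Scheduled contacts.** The row for concomitant therapy and AEs/SAEs in Section 7.3 is marked at Days 0, 28, 56, 91, 182 and 273. The first visit after dosing is Day 28±2.

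**Between visits.** The vaccination questionnaire is marked once, at Visit 2 (Day 28), with footnote f: "To be taken on paper. Subjects will be asked to log all (non-important) AE's between visits".

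**Other routes.** Section 8.2.1 says "All adverse events reported spontaneously by the subject or observed by the investigator or his staff will be recorded". Section 7.7 has the investigators, research physicians and sponsor discuss safety during the study, at no stated interval. Section 8.5 says that there is no DSMB, and Section 9.6 marks interim analysis as not applicable. The SAE reporting times in Section 8.2.2 run from the sponsor's first knowledge of the event.

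**The concern.** A rule that acts on one event is only as fast as the information that feeds it. From 15 minutes after injection until Day 28±2 no one at the site is scheduled to ask the subject anything. The instrument covering those weeks stays on paper with the subject, and its wording does not clearly ask for the events that would trigger the rule.

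The Summary and Section 1.2 describe reactogenicity as arising acutely after injection. The Summary and Section 1.5 describe adverse events as subsiding over days to weeks. A severe early reaction may therefore be over before the first scheduled question about it.

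Two things are at stake. Further subjects may be dosed after an event that should have led to action. The event itself may also be graded and attributed from a four-week recollection, which weakens the record behind the safety endpoint.

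**Working it through.** **1. The gap.** The first scheduled AE contact after dosing is Day 28±2: 28 − 2 = 26 days to 28 + 2 = 30 days.

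**2. The number exposed (the plan's own figure).** Table 2 in Section 4.4 uses a null proportion of 0.70, an alternative of 0.80, one-sided alpha 0.05, power 0.80 and null variance:

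n = [1.645 × √(0.70 × 0.30) + 0.842 × √(0.80 × 0.20)]² / (0.10)² = 118.9, so 119. This matches the plan.

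With 20% drop-out, 119 / 0.80 = 148.75, so 149. The plan rounds this to 150 per cohort, and 4 × 150 = 600.

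**3. The dosing window.** No accrual rate is given. The nearest statement is in Section 3: "The complete study will have a duration of approximately 9-12 months". Subtracting 273 days of follow-up gives:

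- 12 months: 365.25 − 273 = 92 days
- 11 months: 334.8 − 273 = 62 days
- 9 months: 273.9 − 273 = about 1 day

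The lower end leaves no usable window, so the statement cannot fix the accrual rate. The windows below are assumptions.

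**4. Further subjects dosed during the gap.** Under uniform accrual the number is 600 × gap / window.

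| Dosing window | Where it comes from | Gap of 28 days |
|---|---|---|
| 365 days | assumed | 600 × 28 / 365 = 46 |
| 180 days | assumed | 600 × 28 / 180 = 93 |
| 92.25 days | 12-month study less 273 days | 600 × 28 / 92.25 = 182 |
| 61.8 days | 11-month study less 273 days | 600 × 28 / 61.8 = 272 |

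For the 92-day window, gaps of 26 and 30 days give 169 and 195. These figures take an event soon after dosing, no report by the subject before the visit, and enough recruitment left to fill the gap.

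**5. How likely a trigger is.** The document gives no rate. With an assumed true rate p of qualifying events, the chance of at least one is 1 − (1 − p)ⁿ.

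| p | One cohort, n = 150 | All, n = 600 |
|---|---|---|
| 0.1% | 14% | 45% |
| 0.5% | 53% | 95% |
| 1% | 78% | 99.8% |

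**6. What earlier knowledge would change.** As an illustration only, if an event were known after 7 days, the 92-day window would give 600 × 7 / 92.25 = 46 further subjects instead of 182.

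**The case against.** **The log may be meant to be inclusive.** A reader might infer from footnote f that important events are left out. The documents do not establish that. Elsewhere the protocol uses a bracketed qualifier to widen a term: Section 7.6, for example, puts *serious* in brackets to cover serious and other events alike. Footnote f can be read as asking for all events, even trivial ones. The ambiguity stands; exclusion is not shown.

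**Events are also asked about directly.** AEs and SAEs are collected at Day 28, and Section 8.2.1 has subjects monitored from dosing to Day 273. A reaction on Day 2 should therefore be late rather than lost. Loss through poor recall is possible, but systematic under-ascertainment of the safety endpoint does not follow from the text.

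**Subjects can call.** Spontaneous reports are recorded, and an SAE would often surface through hospital care. Advice on when to contact the site may stand in the participant information, which is not in the copy reviewed, so it cannot be said that no such advice exists. This makes Day 28 a worst case. It does not supply a scheduled contact or a stated route in the protocol.

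**The investigators and sponsor review safety.** They do, but at no stated interval, and they can discuss only what has reached them.

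**The count rests on assumed accrual.** This is correct. Taking off a further 2 to 28 days of screening from a 365-day study leaves 90 to 64 days, and so 173 to 244 further injections in 26 days. A reader might take that range as following from the protocol's own figures. It does not, because the duration is approximate and its 9-month end leaves no window. It is one scenario among those tabulated.

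**Earlier experience was mild.** Section 5.4 reports mild AEs and no attributable SAEs. Those were 60 phase I and 52 phase II participants in the study of adjuvanted AKS-452, and the non-adjuvanted booster arm was still under way (Section 1.4).

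**Conclusion.** The point holds as a mismatch between a one-event rule and the data flow that feeds it. Followed as written, the plan can leave a non-serious grade 3 reaction unknown to the investigators for 26 to 30 days while dosing continues. If accrual is uniform and the subject does not report earlier, about 46 further subjects would be dosed in 28 days under a one-year window, about 182 under a 92-day window, and more under a shorter one. The true number depends on an accrual rate that the protocol does not give.

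The different scope of the rule in Sections 4.4 and 7.7 is a separate contradiction. A reader might take it as further evidence of late detection, but it has no bearing on when an event becomes known.

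**What to change.** - **Footnote f.** Reword it to ask for all AEs, including minor ones.
- **Early entries.** Require dated entries with a severity grade for the first days after dosing, the number of days being for the sponsor to set.
- **Collection.** Use a form in REDCap, which already holds the trial data (Section 11.1), with paper as fallback. Section 10.2 already relies on an online survey for pre-screening.
- **Route.** State how an entry at the severity named in the stopping rule reaches the research physicians promptly, before Day 28. A diary still depends on the subject to fill it in, but it removes the wait for the visit. Attribution remains the investigator's judgement under Section 8.2.1.

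Separately, the sponsor must reconcile the per-cohort rule in Section 4.4 with the whole-study rule in Section 7.7. No view is taken here on which should apply.

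The cost is one REDCap form and a change to the footnote and subject instructions, with no extra visit or blood draw. The downside is that the existing study physicians have alerts to read, and some subjects may still need paper.

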#### **7.4 Withdrawal of individual subjects**

Subjects can leave the study at any time for any reason if they wish to do so without any consequences. The investigator can decide to withdraw a subject from the study for urgent medical reasons. In case of drop-outs of this study for any reason, these subjects are kindly asked to complete the follow up period of 273 days for reasons of safety and efficacy. It will also provide the investigators with crucial information about protection against viral infection after multiple vaccine administrations and the AKS-452X booster. The request to complete the follow up will only apply when the subjects have received the AKS-452X booster vaccine.

##### **7.4.1 Specific criteria for withdrawal (if applicable):**

Not applicable.

#### **7.5 Replacement of individual subjects after withdrawal**

Subjects who are withdrawn may be replaced until the intended number of subjects determined by the statistical assessment (i.e. a minimum of 119 subjects per cohort) is reached by this study. The SARS-CoV-2 IgG titer of day 28 can be used for the interim analysis of day 56.

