## 7. METHODS

### 7.1 Study parameters/endpoints

#### 7.1.1 Main study parameter/endpoint

**Main study parameters/endpoints: Primary endpoint:** The percentage of patients that i) achieve an SP/RBD-specific IgG antibody titer level of  $\geq 2.42 \mu\text{g/mL}$  at the day 28 time-point post-intervention (i.e. booster vaccine) if the base-line value prior to receiving the booster vaccine was  $< 2.42 \mu\text{g/mL}$  or ii) where the SP/RBD-specific IgG antibody titer is at least 2x the base-line value prior to receiving the booster vaccine if the base-line value prior to receiving the booster vaccine was  $\geq 2.42 \mu\text{g/mL}$ . The percentage of patients in each of the four cohorts that achieve the primary endpoint threshold at 28 days post-intervention will be calculated (n (%)).

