#### 7.1.2 Secondary study parameters/endpoints

Safety evaluation in the four cohorts for local and systemic adverse events after injection every pre-defined scheduled follow-up (post intervention. Patients will continue to be followed passively for additional safety events out to 9 months post-intervention.

To achieve these objectives, the following will be measured:

- Anti-SARS-CoV-2 SP RBD IgG titers at days 0, 28, 56, 91, 182 and 273 post-boostering.
- Serum titer inhibition of recombinant ACE2-SP/RBD binding and/or neutralization of live SARS-CoV-2 virus infection of live cells (Plaque Reduction Neutralization Test, PRNT) at days 0, 28, and 182
- T-cell responses measured ex vivo using PBMCs to measure SP/RBD-specific T cell production of IFN- $\gamma$  and Th1/Th2/Th17 related cytokines via ELISpot or other Ag-specific flowcytometric-based assays on days 0, 28, and 182.

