**Anti-COVID19 Vaccination AKS-452X BOOSTER Study (Protocol nr. 901452-CT-21-001)**

---

minimum of 119 subjects for final analysis), that have an enhanced immune response as defined as following:

Enhanced immune response rate is defined as:

- i) Seroconversion based on a true positive based on the SP/RBD IgG ELISA assay positive/negative cutoff criteria using the quantitative cut-off value defined by the assay kit batch expressed in  $\mu\text{g/mL}$ . The positive/negative cutoff value was established as  $2.42 \mu\text{g/mL}$  from the validation analysis for the current lot of assay kits, but it should be noted that for each new lot of assay kits, Akston QC performs a re-validation of the cutoff value in order to maintain clinical agreement from lot-to-lot, and/or
- ii) Two times (2x) the baseline SP/RBD IgG at day 56 after a boosting, as compared to the titer at the time of screening (day 0).

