#### 9.4 Secondary study parameter(s)

- To evaluate the inhibitory/neutralization potency of the SP/RBD-specific IgG titers induced AKS-452X and to estimate peak titers and duration of the response.
- To evaluate the Th1/Th2 immune response profile.

To achieve these objectives, the following will be measured:

- Anti-SARS-CoV-2 SP RBD IgG titers at days 0, 28, 56, 91, 182 and 273.
- Serum titer inhibition of recombinant ACE2-SP/RBD binding and/or neutralization of live SARS-CoV-2 virus infection of live cells (Plaque Reduction Neutralization Test, PRNT) at days 0, 28, and 182
- T-cell responses measured ex vivo using PBMCs to measure SP/RBD-specific T cell production of IFN- $\gamma$  and Th1/Th2/Th17 related cytokines via ELISpot or other Ag-specific flowcytometric-based assays on days 0, 28, and 182.

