#### 9.6 Interim analysis (if applicable)

n.a.

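### Section 7.5 lets a Day 28 titer be used for a Day 56 interim analysis that section 9.6 says does not exist; this optional carry-forward could reach the section 7.7 response criterion

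*Protocol*

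**What the plan says.** Protocol section 7.5 has two sentences. The first deals with replacement: "Subjects who are withdrawn may be replaced until the intended number of subjects determined by the statistical assessment", given there as at least 119 per cohort. The second is the rule at issue: "The SARS-CoV-2 IgG titer of day 28 can be used for the interim analysis of day 56". It does not say which subjects it covers, when it applies, or what the Day 56 interim analysis is. Section 9.6, the place for interim analyses, is marked not applicable.

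The protocol uses the two days as follows:

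- **Primary endpoint (7.1.1):** Day 28. The percentage of subjects in each cohort who "achieve the primary endpoint threshold at 28 days post-intervention will be calculated".
- **Response definition for the sample size (4.4):** doubling at Day 28 against Day 0.
- **Cohort criterion (7.7):** at least 80% response is mandatory in each cohort, but the doubling limb reads "Two times (2x) the baseline SP/RBD IgG at day 56 after a boosting". The Summary's Intervention text also uses Day 56.
- **Secondary titers (7.1.2):** "Anti-SARS-CoV-2 SP RBD IgG titers at days 0, 28, 56, 91, 182 and 273 post-boostering". Section 9.4 uses these measurements "to estimate peak titers and duration of the response".

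On drop-out, 7.7 says that "in case a subject dropouts before day 28, he/she will be replaced with another subject". Section 7.4 asks boosted drop-outs to complete follow-up to Day 273, and 7.6 asks for titers after withdrawal where possible.

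**The concern.** Day 28 and Day 56 are separate visits, each with its own blood draw, and the change between them is part of what the secondary objective is meant to describe. Using the earlier value for the later visit treats that change as zero. It also treats a value nobody measured at Day 56 as if it had been.

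The rule is permissive, and the study is open-label with no randomisation. Nothing in the text prevents the choice to substitute from being made after the Day 28 result is known. A fixed rule would at least be applied alike to everyone; an optional one need not be.

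What is at stake is a Day 56 result, not the primary result. The one place where a Day 56 response carries a decision is the mandatory 80% criterion in 7.7. If that criterion is assessed at Day 56 as its doubling limb says, and 7.5 is applied to it, some subjects would be counted on a Day 28 titer.

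**Working it through.** **1. What is not affected.** The cohort size rests on a one-sided one-sample Z test of 0.70 against 0.80, with alpha 0.05 and power 0.80 (section 4.4, Table 2):

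n = [(1.645 × √(0.7 × 0.3) + 0.842 × √(0.8 × 0.2)) / 0.10]² = 118.90, so 119.

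This matches the plan. With 20% drop-out, 119 / 0.80 = 148.75, so 149 against the stated 150, which is close enough. Neither figure depends on Day 56.

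**2. Where the rule can act.**

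| Place | Day | Can the 7.5 sentence reach it? |
|---|---|---|
| 7.1.1, 4.4 | 28 | No |
| 9.6 | none planned | The analysis that 7.5 names is absent |
| 7.7, Summary (Intervention) | 56 | Yes, if this is the assessment 7.5 has in mind |
| 2.2, 7.1.2, 9.4 | 56 as one of six time points | Not by its wording, which names only an interim analysis |

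**3. Size.** Let m be the share of subjects carried forward, r28 the Day 28 responder rate and r56 the true Day 56 rate. Assume the rates are the same in carried and observed subjects. The reported Day 56 rate is (1 − m) × r56 + m × r28, so

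bias = m × (r28 − r56).

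The protocol gives neither r56 nor the share lost between Day 28 and Day 56. I assume r28 = 0.80 (the design value), r56 from 0.60 to 0.90, and m from 2% to 20%. Bias in percentage points:

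| m | r56 = 0.60 | 0.70 | 0.80 | 0.90 |
|---|---|---|---|---|
| 2% | +0.4 | +0.2 | 0 | −0.2 |
| 5% | +1.0 | +0.5 | 0 | −0.5 |
| 10% | +2.0 | +1.0 | 0 | −1.0 |
| 20% | +4.0 | +2.0 | 0 | −2.0 |

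For scale, the standard error of an 80% rate in 119 subjects is √(0.8 × 0.2 / 119) = 3.7 points.

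**4. Which rows are realistic.** The 20% in section 4.4 is total drop-out, not split by visit, in a study that runs to Day 273. Subjects lost before Day 28 have no Day 28 titer to carry and are replaced. Those lost after Day 56 need no substitution. The bottom row is therefore a ceiling.

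**5. Effect on the 80% bar.** With r28 = 0.80 the reported rate is a weighted average of r56 and 0.80, so its expected value moves towards the bar but does not cross it. Crossing in expectation would need r28 above 0.80. Otherwise substitution decides the outcome only when the count is already close to the bar: 0.80 × 119 = 95.2, so 96 responders.

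**The case against.** The strongest reply is that the sentence has nothing to act on. It licenses substitution only for an interim analysis, and section 9.6 says there is none. The Day 56 review that the protocol does describe belongs to the earlier phase I trial, so the line may be leftover text, as the phase I heading of section 7.3 appears to be. It could also mean only that Day 28 titers feed a look held around Day 56, with no value relabelled. The primary endpoint is at Day 28, and 7.4 and 7.6 show that real later titers are sought from drop-outs.

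Much of this stands, and it limits the point to a minor one. It does not remove it, because 7.7 still states a mandatory criterion with a Day 56 limb and 7.5 still permits a Day 28 value at Day 56. Leftover text in a governing document is still text that someone may apply.

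A reader might go further in three ways that the documents do not support:

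- **That the rule hides waning or overstates response.** No human titers between Day 28 and Day 56 after the booster are given. The mouse boost data in section 1.4 show about 3.5-fold at two weeks and about 4-fold at Day 70, which is no fall. The Summary's general expectation that immunity will not last long gives no figure for this interval.
- **That a fifth of each cohort would be carried forward.** The 20% is not a loss between Day 28 and Day 56.
- **That a withdrawn subject and the replacement would both be counted.** Section 7.7 describes replacement for losses before Day 28, and those subjects have nothing to carry. The text does not rule out double counting, but it does not provide for it either.

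**Conclusion.** The point holds as a cheap improvement. Section 7.5 states an optional, unconditioned substitution for an analysis the protocol elsewhere says is not planned, while 7.7 leaves a Day 56 decision that the substitution could enter. The words themselves do not limit the rule to withdrawn subjects; that limit comes from the section heading.

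The bias would be upward if titers fall after Day 28, downward if they rise, and nil if they stay level. Under the assumed range it runs from +4.0 to −2.0 points at the 20% ceiling. At 2% to 5% carried it runs from +1.0 to −0.5 points, well inside one standard error. These figures rest on an assumed Day 28 rate of 80%, assumed Day 56 rates of 60% to 90%, and equal rates in carried and observed subjects. Substitution chosen with knowledge of the Day 28 result is not covered by them.

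The firmer defects are the contradictions that make the sentence usable: 7.5 against 9.6 on whether an interim exists, and 4.4 and 7.1.1 against 7.7 and the Summary's Intervention text on whether doubling is judged at Day 28 or Day 56.

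**What to change.** Delete the second sentence of section 7.5 and put in its place:

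> Each titer is analysed only at the visit at which it was drawn. A Day 28 titer is not substituted for Day 56 or any later visit. Day 56 responder percentages are based on subjects with an observed Day 56 titer, and that number is reported.

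Then reconcile two pairs of statements:

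1. Sections 7.5 and 9.6. If no interim is planned, remove the reference to one. If one is, define it in 9.6.
2. The response day in 4.4 and 7.1.1 against that in 7.7 and the Summary's Intervention text, so that the 80% criterion has one time point.

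No extra subjects, samples or visits are needed, and the sample size does not change. The cost is a slightly smaller Day 56 denominator. How later titers are modelled can be left to the statistical analysis plan.
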